1. Provide a sample size and a justification as to how you arrived at that number. If you use screening procedures to arrive at a final sample a table may be helpful.

Pilot Study:

We have chosen to include 60 women in the measurement validation and pilot intervention phase because this sample size will allow for each pair of facilitators (5 pairs in total) to run through the entire intervention starting with 12 women each. Sixty participants is also a sufficient sample size to meet the objectives of our measurement validation activities.

Randomized Controlled Trial:

Our primary outcomes are both assessed on a continuous scale, thus we conducted a sample size calculation for the randomized controlled trial intended for two-sample mean comparisons using one of our primary outcomes of interest, psychological distress. We gathered information from previous trials measuring our primary outcome(s) of interest in similar populations to estimate the following parameters used for the sample size calculation:

$$\sigma_{time1}^{2}=0.25$$

$$\sigma_{time2}^{2}=0.36$$

$$\rho=0.333$$

$$\sigma_{change}^{2}=0.55007$$

$$m=10$$

$$\mu_{1}=1.3$$

$$\mu_{2}=0.7$$

$$N=\frac{2\left( z_{\frac{\alpha}{2}}+z_{\beta} \right)^{2}(\sigma^{2})(1+\left( m-1 \right)\rho)}{{(\mu_{1}-\mu_{2})}^{2}}=\frac{2\left( 1.96+0.842 \right)^{2}(0.55007)(1+\left( 18.269-1 \right)0.333)}{{(1.3-0.7)}^{2}}=161.97$$

In order to have 80% power to detect a treatment effect of similar magnitude as previous trials that are roughly comparable in terms of intervention and population at the 0.05 significance level, we need 162 persons per group. To account for 10% attrition, we will recruit a target sample of 180 participants per group (360 total).

Process Evaluation:

We will conduct a total of 28 qualitative interviews as part of the process evaluation. We will recruit a subset of the participants that were enrolled in the randomized controlled trial (n=10) to participate in the process evaluation. We will recruit 10 intervention facilitators, their clinical supervisor (n=1) and 7 members of local partner organization to interview regarding implementation facilitators and challenges. These new participants will not be interviewed regarding personal health information and the focus of the interviews will be on program implementation.

Total Sample Size:

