**IV. Participants**

Describe the study participants and the population from which they will be drawn. Specify the inclusion and exclusion criteria. If you plan to include children, note their ages and whether you will include children in foster care. Note if the participants are particularly vulnerable in terms of cognitive limitations, education, legal migration status, incarceration, poverty, or some combination of factors.

Congolese refugee women residing in Nyarugusu camp in northwest Tanzania reporting a past-year history of intimate partner violence and experiencing moderate to severe psychological distress will be included in this study. We will initially invite women to participate that are members of women’s groups that operate throughout the camp. Women’s groups in Nyarugusu have been organized as a mechanism to strengthen social support among women in the camp. The types of women’s groups include cooking, weaving, tailoring and microfinance. Women’s groups are formed by IRC and other agencies in the camp; however, women from the community may propose to start a women’s group to these agencies as well. Each women’s group contains approximately 11-20 women and they each elect a leader that organizes group meetings and activities throughout the camp. Members organize most women’s group activities, however IRC and other agencies do occasionally provide skills trainings to women’s groups at the women empowerment center or other venues throughout the camp. In addition to recruitment through women’s groups, we will also include women that are referred to the program so long as they meet the following eligibility criteria:

1. Inclusion criteria:
   1. 18+ years of age
   2. Female
   3. Refugee from the DRC residing in Nyarugusu refugee camp
   4. Past-year history of intimate partner violence (survivor)
   5. Experiencing moderate to severe levels of psychological distress during the past month as measured by the 25-item Hopkins Symptom Checklist and the Harvard Trauma Questionnaire (Average Score >=1.75 on either checklist, indicating close to a moderate amount of distress)
2. Exclusion criteria:

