The primary goal of the study is to evaluate whether levels of psychological distress, intimate partner violence and/or functional impairment differ by exposure to the experimental intervention. To assess this quantitatively we will construct multilevel mixed effects models that account for the clustered design (within women’s groups) and allow for longitudinal analysis of the changes in these outcomes (while accounting for within-person clustering). Given that this is a randomized controlled trial, we do not anticipate any pre-treatment confounding, but will evaluate the similarity between groups in terms of important covariates at baseline. We are also including measures of hypothesized mediators and moderators of intervention efficacy that will be analyzed as our secondary analyses.

1. Describe whether you are collecting or storing personal identifiers, and if yes, why you need them, and when and how you plan to dispose of them. Signatures on consent forms are considered to be identifiers.

There are two points in the program at which we collect and store personal identifiers. The first is after the screening at which time we ask for the participant’s contact information to allow for communication with the participant throughout the follow-up period, as well as a signature (or thumbprint) on the consent forms. Immediately following the interview, this information will be placed in a double-lock safe in the research team office. The in-country project coordinator will input this information into a password-protected file that connects the participants alphanumeric ID with their name and contact information. This is the only place that this information will be connected. Afterwards, the physical contact sheet will be shredded. The consent forms will also contain personal identifiers. These consent forms will also be kept in the double-lock safe in the research team office.

6. Answer the following **if they are relevant to your study design**:

a. If the study has different arms, explain the process for assigning participants (intervention/control, case/control), including the sequence and timing of the assignment.

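### On the inputs substituted into the sample-size formula, 162 women per group are about nine women's groups per arm and give about 75% power, not 80%; the cluster size and change variance must be settled before any power can be stated

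*Protocol*

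**What the plan says.** Section III (sample size, Randomized Controlled Trial) lists variances of 0.25 and 0.36 at the two times, rho = 0.333, a change variance of 0.55007, m = 10, and means of 1.3 and 0.7. The worked formula multiplies the usual two-sample expression by the design effect 1+(m-1)rho. It uses the normal quantiles 1.96 and 0.842 and substitutes 18.269 for m, not the listed 10. The result is 161.97. The text then reads "In order to have 80% power to detect a treatment effect of similar magnitude as previous trials" and, further on, "at the 0.05 significance level, we need 162 persons per group". Recruitment is set at 180 per group (360 in total) to allow for 10% attrition.

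Women's groups are the unit of randomization. Section IV says that each "group contains approximately 11-20 women", and that only women with past-year intimate partner violence and raised distress scores are eligible. Section V.C plans "multilevel mixed effects models that account for the clustered design". Neither the number of women's groups to be randomized nor any measure of variation in cluster size is stated.

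**The concern.** In a cluster-randomized comparison, the precision of the between-arm variance estimate depends on the number of clusters, not the number of women. With fewer than ten clusters per arm, the critical value is clearly above 1.96, and a calculation with normal quantiles returns too small a sample. A single cluster size also ignores variation between groups, which increases the design effect. The 80% figure justifies enrolling 360 women, so a reader needs to know whether the design that the formula describes delivers it.

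**Working it through.** **Inputs (all from section III unless noted).** Difference 1.3 - 0.7 = 0.6; variance of change 0.55007; rho 0.333; m = 18.269 as substituted, 10 as listed; quantiles 1.96 and 0.842; 10% attrition. Women's group size 11-20 (section IV).

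**1. The protocol's own figure.** Design effect = 1 + 17.269 x 0.333 = 6.7506. N = 2 x 2.802² x 0.55007 x 6.7506 / 0.36 = 161.97. This reproduces. With m = 10 the design effect is 3.997 and N = 95.9, which does not.

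**2. Number of clusters implied.** k = 162 / 18.269 = 8.87 women's groups per arm. Degrees of freedom 2k - 2 = 15.7; two-sided 5% critical value 2.12.

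**3. Power on the substituted inputs.** Standard error = √(2 x 0.55007 x 6.7506 / 162) = 0.2141. Noncentrality = 0.6 / 0.2141 = 2.802. Noncentral t power on 15.7 df = **74.8%**, against 80% from normal quantiles.

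**4. Unequal clusters.** Design effect 1 + ((1 + CV²)m - 1)rho. Sizes uniform over 11-20 have mean 15.5 and CV 0.185. Then the design effect is 6.96 and power **73.5%**. This is illustrative, because 18.269 is above that mean.

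**5. If 18.269 is the recruited size.** 180 / 18.269 = 9.85 groups per arm, and 162 / 9.85 = 16.44 women analysed per group. Power is **79.3%** with equal clusters and **78.1%** at CV 0.185.

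**6. Sensitivity to the two conflicting inputs (162 analysed per arm, t-based).**

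| m | Variance of change | Groups per arm | Power, CV 0 | Power, CV 0.3 (assumed) |
| --- | --- | --- | --- | --- |
| 18.269 | 0.55007 | 8.9 | 74.8% | 71.5% |
| 10 | 0.55007 | 16.2 | 94.1% | 92.5% |
| 18.269 | 0.4102 | 8.9 | 86.0% | 83.3% |
| 10 | 0.4102 | 16.2 | 98.3% | 97.6% |

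The value 0.4102 is 0.25 + 0.36 - 2 x 0.333 x 0.5 x 0.6, taking the listed rho as the correlation between the two times. The printed value agrees, to rounding, with 0.61 - 2 x 0.333 x 0.25 x 0.36 = 0.55006, which multiplies variances where standard deviations belong. If rho is meant only as the intracluster correlation, 0.55007 needs a pre-post correlation of (0.61 - 0.55007) / (2 x 0.5 x 0.6) = 0.10, which is not listed.

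**7. Does the method error depend on m?** No. At m = 10 the same formula would stop at 96 per arm, or 9.6 groups, where t-based power is 75.3%. The formula ends at nine to ten clusters per arm with either value.

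**The case against.** The strongest reply is that the shortfall depends on inputs that the protocol itself contradicts. This stands. Nine groups per arm follows only from 18.269, which appears once, in the substitution. The listed m = 10 gives 16.2 groups per arm and about 94% power at 162. With the change variance implied by the listed variances and rho, power exceeds 80% even at m = 18.269.

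A reader might infer that the trial's true power is 71-75%. The documents do not support that. The lower end needs a CV near 0.3, which would have to come from partial enrolment of groups of 11-20 women. Partial enrolment also makes clusters smaller than the 15.5 mean, not as large as 18.269. Matched pairs give more: 82.5% at m = 14 with CV 0.3, and 80.4% at m = 15.5 with CV 0.185 (variance 0.55007). Referred women could enlarge clusters, but the protocol gives no number and expects most participants to come from women's groups.

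A reader might also infer inflated type I error in the analysis. The protocol names a multilevel model but no degrees-of-freedom method. A statistical analysis plan may set one, so this is not a finding.

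What the reply does not remove is the method error: correcting m alone would still leave normal quantiles in use at nine to ten clusters per arm.

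**Conclusion.** The concern holds in conditional form. On the inputs that produce 162, the stated 80% is wrong: power is about 75% with equal clusters and about 73.5% with sizes spread uniformly over 11-20. It is about 78-79% if 18.269 is the recruited cluster size and the 10% loss falls evenly within groups. The loss is therefore about one to six percentage points, depending on the reading. The equal-cluster figure of 74.8% needs no assumption beyond the substituted values; the others rest on the stated CV or on how attrition falls.

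This does not show that the trial is underpowered. Two other conflicts in the same calculation, m of 10 against 18.269 and variance 0.4102 against 0.55007, each move power upward by more than this error moves it down. The protocol as written supports no single power figure.

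**What to change.** In section III:

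- Settle one expected cluster size (10 or 18.269), say whether it counts women recruited or women analysed, and use it in both the list and the formula.
- Correct the change variance, or list the pre-post correlation that yields it. Label that correlation separately from the intracluster correlation.
- State the number of women's groups per arm, k.
- Recompute with t quantiles on 2k - 2 degrees of freedom and design effect 1 + ((1 + CV²)m - 1)rho, with a CV consistent with the chosen cluster size.
- Restate the power that 360 women give.

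The cost is a few lines of recalculation. If 18.269 and 0.55007 both stand, the stated power becomes less favourable; otherwise it probably rises. No extra participants are required, because the change is to the stated power and not to the enrolment target.

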We plan to conduct a cluster randomized controlled trial evaluating the efficacy of the aforementioned integrated mental health treatment and intimate partner violence prevention intervention as compared with a treatment as usual control group. In Nyarugusu Refugee Camp, the setting of this study, there are 7 zones within which refugees live. These zones are further subdivided into 52 villages. Women’s groups (described in further detail below; section IV. Participants) operate within these villages and will serve as the site of recruitment and the unit of randomization. Women entering the trial will be assessed for symptoms of mental health problems, intimate partner violence and other related constructs at baseline (week 1) and one post-intervention follow-up at week 10. All measurement and data collection is based on self-report indicators reported by the participant. The intervention is designed to last approximately 2 months (8 sessions, once per week for 8 weeks) with full participation in the study lasting 10 weeks (baseline to follow-up).

AIM 4: Conduct a qualitative process evaluation to examine facilitators and barriers to implementation of the research and intervention protocols.

We plan to conduct a qualitative process evaluation of the implementation of the Nguvu intervention and research protocols within the context of the randomized controlled trial described in Aim 3. To do so we will recruit a subset of participants (n=10), both high (n=5) and low attenders (n=5) from the intervention condition to participate in a qualitative interview with a member of the research team to discuss their experience participating in the intervention related to perceived challenges, risks, benefits, operations and acceptability. We will also qualitatively interview the 10 intervention facilitators and their clinical supervisor to identify their perspectives on successes and challenges of the intervention as well as their experiences as a provider of these services. Lastly, we will conduct qualitative interviews with seven representatives from partner agencies and the community advisory board to examine structural challenges to implementation as well as the perceived impact that implementing Nguvu had at the community and organizational level. We estimate that each of these interviews will take approximately one hour to complete and will be delivered by our trained research assistant team.

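### The 162 women per group for 80% power does not follow from the listed parameters: two cluster sizes are given, and one undefined rho appears to serve two purposes

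*Protocol*

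**What the plan says.** The trial is cluster-randomised. Women's groups "will serve as the site of recruitment and the unit of randomization" (Protocol, III. Study Design, Aim 3).

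The sample size item in the same section describes a calculation for "two-sample mean comparisons using one of our primary outcomes of interest, psychological distress". It lists these parameters as used: variances of 0.25 at time 1 and 0.36 at time 2, rho = 0.333, "\sigma_{change}^{2}=0.55007", m = 10, and means of 1.3 and 0.7. The worked formula then contains "18.269-1 \right)0.333" in the design effect, so the cluster size substituted is 18.269. The result is 161.97, and the text concludes: "In order to have 80% power to detect a treatment effect of similar magnitude as previous trials" of a roughly comparable kind, with a significance level of 0.05, "we need 162 persons per group. To account for 10% attrition, we will recruit a target sample of 180 participants per group (360 total").

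Rho is not defined in words, and no other correlation is listed. On cluster membership, IV. Participants says that each women's group "contains approximately 11-20 women". The number of groups per arm is not given.

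**The concern.** This is the protocol's only power statement and its only basis for enrolling 360 women. A reader who takes the listed parameters at face value does not get 162, and a reader who takes the printed formula has to accept a cluster size with no source.

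With an intracluster correlation as large as 0.333, the design effect depends strongly on m: it is 4.0 at m = 10 and 6.75 at m = 18.269. Which m was meant is therefore not a detail.

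The variance of change raises a second doubt. It depends on the correlation between a woman's two measurements, which is a different quantity from the correlation between women in the same group. Only one symbol and one value are offered for both.

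**Working it through.** **Inputs** (all from III. Study Design, sample size item): z values 1.96 and 0.842; variances 0.25 and 0.36, so SDs 0.5 and 0.6; rho = 0.333; change variance 0.55007; m = 10 as listed, 18.269 as substituted; mean difference 1.3 − 0.7 = 0.6.

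**1. The protocol's figure.** N = 2(1.96 + 0.842)² × variance × (1 + (m − 1)rho) / 0.6².

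- Without the design effect: 2 × 7.8512 × 0.55007 / 0.36 = 23.993.
- Design effect as printed: 1 + 17.269 × 0.333 = 6.7506.
- N = 23.993 × 6.7506 = 161.97. This reproduces the printed result.
- Attrition: 162 / 0.9 = 180. Correct.

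**2. The listed cluster size.** Design effect 1 + 9 × 0.333 = 3.997, so N = 23.993 × 3.997 = 95.9, or 96 per group. That is 41% below 162.

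**3. The change variance.** The formula is variance 1 + variance 2 − 2 × r × SD1 × SD2, where r is the pre-post correlation.

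- With r = 0.333: 0.61 − 2(0.333)(0.5)(0.6) = 0.61 − 0.1998 = 0.4102.
- With variances in place of SDs: 0.61 − 2(0.333)(0.25)(0.36) = 0.61 − 0.05994 = 0.55006. The listed value is 0.55007; any rho from about 0.33292 to 0.33297, which rounds to 0.333, returns it exactly.
- If 0.55007 was instead obtained by the correct formula, it implies r = (0.61 − 0.55007) / (2 × 0.5 × 0.6) = 0.0999, a value the protocol does not state.

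**4. Required N, and power with 162 analysed per group.** Normal-approximation power is Φ(0.6/SE − 1.96), with SE = √(2 × variance × design effect / 162). For the printed values SE = 0.2141 and 0.6/0.2141 − 1.96 = 0.842, which is 80.0%. The last column uses a noncentral t with 2k − 2 degrees of freedom, where k = 162/m clusters per arm (8.9 at m = 18.269; 16.2 at m = 10).

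| Change variance | m | N per group | Power, normal | Power, t |
|---|---|---|---|---|
| 0.55007 | 18.269 | 162 | 80.0% | 74.8% |
| 0.55007 | 10 | 96 | 95.4% | 94.1% |
| 0.4102 | 18.269 | 121 | 90.1% | 86.0% |
| 0.4102 | 10 | 72 | 98.8% | 98.3% |

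All rows keep 0.333 as the intracluster correlation. With variance 0.55007, normal-approximation power falls below 80% only if m exceeds 18.269; at m = 20, the top of the stated membership range, it is 76.7%.

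**The case against.** The strongest reply is that the printed line is correct. If 18.269 was the working value and m = 10 is a stale entry in the list, 162 and 80% stand by the protocol's own formula. This is fair as far as it goes: the figure can be reproduced, and a reader who concludes that it cannot goes too far. But the text does not show which m is stale, and it gives no basis for 18.269.

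It can also be said that rho is used only as the intracluster correlation, so nothing listed contradicts 0.55007. That reading is open. It leaves 0.55007 resting on an unstated pre-post correlation of about 0.10, and it makes the near-exact match in step 3 a coincidence. The match is an inference about how the number arose, not something the protocol says.

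Three stronger readings are tempting but not supported.

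- A reader might infer that the trial is underpowered. Correcting m to 10, the variance to 0.4102, or both lowers the required N.
- A reader might infer that 18.269 cannot be the number enrolled per group. It is improbable, because it would take nearly all members of groups near the top of the range, before eligibility and consent. It is not impossible: the range is approximate, and referred women outside the groups may also be enrolled (IV. Participants; V.A Recruitment Process).
- A reader might infer that the wrong number of groups will be randomised. The protocol derives no group count from m; V.C, item 6a, says only that the camp's women's groups will be randomised before recruitment.

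**Conclusion.** The concern holds in this form: 162 per group for 80% power is not a consequence of the listed parameters. The conflict between m = 10 and m = 18.269 is certain and moves the requirement from 162 to 96 per group, or the power at 162 from 80% to about 95%. The double use of rho is probable. If 0.333 is the pre-post correlation, the change variance is 0.4102, and the requirement is 121 per group at m = 18.269 or 72 at m = 10.

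By the protocol's formula 162 is therefore probably conservative, assuming an intracluster correlation of 0.333 and a difference of 0.6. One qualification runs the other way. If the printed values are right, there are only about 9 clusters per arm, and a t reference on cluster degrees of freedom gives about 75%, so even then 80% is not secure. The defect lies in the power statement and its inputs; it does not show that 360 is the wrong number.

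**What to change.** In the sample size item of III. Study Design:

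1. Give the intracluster correlation and the pre-post correlation separate symbols, values and sources.
2. Recompute the change variance from the pre-post correlation with standard deviations in the covariance term.
3. Use one m throughout, equal to the number of women expected to be enrolled and analysed per women's group after eligibility and consent, and state its basis.
4. State the resulting number of groups per arm, and use a t reference if that number is small.
5. Restate the power for the planned 360 women, that is 324 analysed (162 per group) after 10% attrition.

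The cost is one recalculation and a changed power statement. No change in enrolment is proposed.

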**IV. Participants**

Describe the study participants and the population from which they will be drawn. Specify the inclusion and exclusion criteria. If you plan to include children, note their ages and whether you will include children in foster care. Note if the participants are particularly vulnerable in terms of cognitive limitations, education, legal migration status, incarceration, poverty, or some combination of factors.

Congolese refugee women residing in Nyarugusu camp in northwest Tanzania reporting a past-year history of intimate partner violence and experiencing moderate to severe psychological distress will be included in this study. We will initially invite women to participate that are members of women’s groups that operate throughout the camp. Women’s groups in Nyarugusu have been organized as a mechanism to strengthen social support among women in the camp. The types of women’s groups include cooking, weaving, tailoring and microfinance. Women’s groups are formed by IRC and other agencies in the camp; however, women from the community may propose to start a women’s group to these agencies as well. Each women’s group contains approximately 11-20 women and they each elect a leader that organizes group meetings and activities throughout the camp. Members organize most women’s group activities, however IRC and other agencies do occasionally provide skills trainings to women’s groups at the women empowerment center or other venues throughout the camp. In addition to recruitment through women’s groups, we will also include women that are referred to the program so long as they meet the following eligibility criteria:

1. Inclusion criteria:
   1. 18+ years of age
   2. Female
   3. Refugee from the DRC residing in Nyarugusu refugee camp
   4. Past-year history of intimate partner violence (survivor)
   5. Experiencing moderate to severe levels of psychological distress during the past month as measured by the 25-item Hopkins Symptom Checklist and the Harvard Trauma Questionnaire (Average Score >=1.75 on either checklist, indicating close to a moderate amount of distress)
2. Exclusion criteria:
   1. Serious mental illness including intellectual disabilities that would preclude comprehension of intervention material, psychotic symptoms (e.g. hallucinations, delusions), manic symptoms and severe substance use problems (i.e. intoxication at the time of screening). Note: Participants meeting this exclusion criterion will be referred to the mental health clinic at the Tanzania Red Cross Hospital or to an IRC counselor/case manager for further assessment and referral.
   2. Imminent risk of suicide. Note: Participants meeting this exclusion criterion will be referred to one of the eight IRC counselors we have trained in suicide risk management. Research assistants are instructed to not leave participants meeting this exclusion criterion alone, if possible, until they are in the presence of the on-call IRC counselors trained in suicide risk management.

*Process Evaluation:* Ten of the participants in the process evaluation will be a random sample of high- (n=5) and low-attenders (n=5) from the Nguvu treatment condition and will thus meet the eligibility criteria described above. The eligibility criteria for the remaining 18 participants are as follows:

1. N=10: Nguvu facilitators that were trained by study staff to administer the Nguvu intervention as part of the randomized controlled trial.
2. N=1: Clinical supervisor to the Nguvu facilitators during the randomized controlled trial period
3. N=1: Field manager of the Nguvu research team
4. N=1: Focal point for protection and/or health at the UNHCR (partner agency) Kasulu field office
5. N=2: IRC (partner agency) gender-based violence program focal points in Nyarugusu camp
6. N=1: IRC (partner agency) focal points in Kasulu office
7. N=2: Community advisory board members in Nyarugusu

**NOTE**: If you are recruiting participants or receiving, accessing, or using data from a U.S. health care provider, HIPAA review is likely to be required. If you plan to bring identifiable health information from a foreign country to a U.S. covered entity (e.g., lab at the Hopkins SOM), HIPAA may be triggered. Check “yes” to the HIPAA question in the PHIRST application.

